## Abstract

**Background:**

Post–COVID-19 condition is emerging as a new epidemic, characterized by the persistence of COVID-19 symptoms beyond 3 months, and is anticipated to substantially alter the lives of millions of people globally. Patients with severe episodes of COVID-19 are significantly more likely to be hospitalized in the following months. The pathophysiological mechanisms for delayed complications are still poorly understood, with a dissociation seen between ongoing symptoms and objective measures of cardiopulmonary health. COVID-19 is anticipated to alter the long-term trajectory of many chronic cardiovascular and pulmonary diseases, which are common among those at risk of severe disease.

**Objective:**

This study aims to use a single, integrated device—MouthLab, which measures 10 vital health parameters in 60 seconds—and a cloud-based proprietary analytics engine to develop and validate the Aidar Decompensation Index (AIDI), to predict decompensation in health among patients who previously had severe COVID-19.

**Methods:**

Overall, 200 participants will be enrolled. Inclusion criteria are patients in the US Department of Veterans Affairs health care system; “severe” COVID-19 infection during the acute phase, defined as requiring hospitalization, within 3-6 months before enrollment; aged ≥18 years; and having 1 of 6 prespecified chronic conditions. All participants will be instructed to use the MouthLab device to capture daily physiological data and complete monthly symptom surveys. Structured data collection tables will be developed to extract the clinical characteristics of those who experience decompensation events (DEs). The performance of the AIDI will depend on the magnitude of difference in physiological signals between those experiencing DEs and those who do not, as well as the time until a DE (ie, the closer to the event, the easier the prediction). Information about demographics, symptoms (Medical Research Council Dyspnea Scale and Post-COVID-19 Functional Status Scale), comorbidities, and other clinical characteristics will be tagged and added to the biomarker data. The resultant predicted probability of decompensation will be translated into the AIDI, where there will be a linear relationship between the risk score and the AIDI. To improve prediction accuracy, data may be stratified based on biological sex, race, ethnicity, or underlying clinical characteristics into subgroups to determine if there are differences in performance and detection lead times. Using appropriate algorithmic techniques, the study expects the model to have a sensitivity of >80% and a positive predicted value of >70%.

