### Sample Size

To develop the AIDI algorithm, the study will collect longitudinal parameters that lead up to a DE with the MouthLab device. Because the actual multiparametric changes are unknown and are, in fact, the outcome of the study, the study aims to obtain as much data as possible from those who experience a DE. For this study, we estimate that 100 individual DEs would be sufficient to create a statistical algorithm to predict decompensation. The ultimate goal is to have the algorithm produce no false negatives (ie, if someone is at risk of decompensation while the algorithm says that they are not) and less than 10% false positives (ie, if someone is *not* at risk of decompensation while the algorithm says they are). That is, we do not want to miss any DEs at the cost of having some nonevents classified as being risky.

Al-Aly Z et al [11] observed that the risk and associated burden of pulmonary and extrapulmonary manifestations increase across the disease spectrum of acute COVID-19 infection (from nonhospitalized individuals to hospitalized individuals and then to those admitted to intensive care). The study implemented a comparative approach to examining postacute sequelae in individuals who are hospitalized with COVID-19 versus individuals with seasonal influenza (using a high-dimensional approach and through examination of prespecified outcomes). Results suggested that there is a substantially higher burden of a broad array of postacute sequelae in the individuals who are hospitalized with COVID-19, which provides features that differentiate post–COVID-19 condition (both in the magnitude of risk and the breadth of organ involvement) from postinfluenza viral syndrome [11]. A study by Mainous et al [2] demonstrated a hospitalization rate of 29.8% among survivors of “severe COVID-19.” Given that the AIDI study has defined “decompensation” more broadly than hospitalization alone, we anticipate higher decompensation rates among our study population. Conservatively estimating 1 DE per any participant, with an event rate of 60%, we would need 168 participants to complete the study in order to capture 100 DEs. Since we anticipate up to 15% dropout, we will aim to recruit 200 participants.

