### Statistical Analysis

#### Feature Engineering and Selection

For each patient, baseline readings will be based on their first few MouthLab measurements. The number of observations used to establish the baseline will depend on the variability in each patient’s reading. We will then summarize the patient’s parameters obtained from the MouthLab data collection. At each time t, we will include the most recent observations, changes since the last reading, trends, variability in values, and comparison to the patient’s baseline. Additionally, we will include information about demographics, symptom scores, other clinical characteristics, as well as key comorbidities. We anticipate that variable interactions will be important. Given the cohort size and the number of different features, regularization will be applied to avoid overfitting.

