#### Outcome Modeling

We will define the outcome as patients experiencing a DE within τ time units (DEτ). For different values of τ, we will deploy a series of more sophisticated models in order to explore the predictive ability of different approaches, as detailed below. We will split up the data into training and testing datasets based on the time of enrollment. We anticipate an 80:20 split; in other words, we will set aside 20% of the data to evaluate the model performance. For each τ, we will construct a training dataset consisting of multiple overlapping time segments for each patient, which we refer to as the observation period (eg, 2 weeks), and multiple nonoverlapping time segments leading up to the outcome for the patients that experience the outcome, one of which contains the outcome.

Second, we will explore several other machine learning algorithms, including classification trees, random forest, and boosting approaches, to understand whether these more flexible modeling approaches have an advantage over the logistic regression approach. The output of any of these approaches is a predicted probability of a DE occurring within the following τ days given observations of a fixed observation interval (eg, up to 30 previous measurements, or ~2 weeks). As stated earlier, the goal is to develop the AIDI to predict worsening health. The detailed analysis laid out above will allow us to understand the ability of early prediction, that is, the critical time frame just prior to decompensation during which the probability of hospitalization becomes increasingly predictive.

The initial exploratory analysis will inform the selection of proper features for the analysis. We will model the patient’s risk of hospitalization as a function of their physiological values, short-term changes in those values, changes from the baseline, etc. The initial exploratory analysis will inform features such as the appropriate time ranges (eg, should short-term changes be captured since the last reading or over the last 24 hours).

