#### Performance Evaluation

In case of a lower-than-expected number of observed outcomes, or smaller differences than expected between those who experience the outcome and those who do not, we may revert from our 80:20 split to use cross-validation to measure performance. In that case, we will evaluate the algorithm using the leave-one-out cross-validation technique. We will implement this approach by leaving out one patient at a time (corresponding to potentially multiple observation periods to avoid fitting the model on data from the same patient as the model is being evaluated). The leave-one-out cross-validation technique facilitates cross-validation evaluation of the algorithm structure to assess its robustness to changes. This validation step will remake the algorithm for every patient left out of the algorithm development iteration. In short, this approach fits each algorithm using all available data except for (in our case) the data of one patient and then summarizes whether the algorithm predicts the correct classification of decompensation or nondecompensation for each observation period. This process is repeated over all available patients. For each τ, we will summarize the accuracy, false positives, and false negatives.

The resulting predicted probabilities of decompensation will then be translated into the easy-to-communicate AIDI, where there is a linear relationship between the risk score and the AIDI. At the conclusion of phase 3, the final COVID-19 DE detection performance of the AIDI will be evaluated using standard measures including sensitivity, specificity, and positive predictive value across a wide range of risk cutoff values. Overall, AIDI DE detection performance and lead time statistics will be examined across study populations as well as within subgroups. If necessary, to improve prediction accuracy, data may be stratified based on biological sex, race, ethnicity, or underlying clinical characteristics into subgroups to determine if there are differences in performance and detection lead times among the groups.

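### The stated AIDI performance measures do not separate stable between-patient risk from a within-patient rise before a DE, and the sensitivity and PPV targets carry no unit or τ

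*Protocol article*

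**What the plan says.** Protocol article, Abstract (Methods): performance will depend on the "magnitude of difference in physiological signals between those experiencing DEs and those who do not", and the sentence continues "as well as the time until a DE (ie, the closer to the event, the easier the prediction". The abstract also states that "the study expects the model to have a sensitivity of >80% and a positive predicted value of >70" percent. No unit and no τ are attached to these figures.

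Sample Size gives a different pair, described as the ultimate goal: "no false negatives (ie, if someone is at risk of decompensation while the algorithm says that they are not) and less than 10% false positives". It assumes one DE per participant and a 60% event rate.

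Feature Engineering and Selection: "At each time t, we will include the most recent observations", together with changes, trends, variability and comparison with the patient's own baseline. Demographics, symptom scores, clinical characteristics and comorbidities also enter.

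Outcome Modeling: "We will define the outcome as patients experiencing a DE within τ time units (DEτ"). τ is left open. The training data take several segments from each patient with a DE, only one of which contains it. The declared purpose is to find "the critical time frame just prior to decompensation during which the probability of hospitalization becomes increasingly predictive".

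Performance Evaluation: classification is scored per observation period in the description of leave-one-out cross-validation, which is the fallback from the 80:20 split. Accuracy, false positives and false negatives are summarised for each τ. Final detection performance is given as sensitivity, specificity and PPV over a range of cutoffs, plus lead-time statistics, with no unit named.

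**The concern.** The question in Outcome Modeling is temporal: when does a patient who will decompensate begin to look different? Pooled measures mix two sources of discrimination. One is stable risk, where sicker patients score higher throughout. The other is warning, where a patient's score rises shortly before the DE. The model may use both, which is legitimate for prediction, but only the second supports a claim of early warning.

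Lead time does not resolve this, because a score that is high from the first day has the longest lead time of all. If the targets may also be counted per patient, an index that only marks the chronically ill could be reported as meeting them.

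**Working it through.** **The plan's own figures.** 100 / 0.60 = 166.7, so 167 completers, against 168 stated (168 × 0.60 = 100.8 DEs). 168 / 0.85 = 197.6, so 198, against 200 stated. Both agree.

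**Targets counted per patient.** Inputs: prevalence p = 0.60 (Sample Size), sensitivity 0.80 and PPV 0.70 (Abstract). PPV = Se·p / [Se·p + FPR·(1 − p)], so the largest false-positive rate allowed is

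FPR = 0.80 × 0.60 × (0.30/0.70) / 0.40 = 0.514, that is, specificity 0.486.

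With equal-variance binormal scores, d′ = z(0.80) − z(0.514) = 0.806, and AUC = Φ(0.806/√2) = 0.716. A score fixed for six months with that AUC meets both targets. Flagging everyone already gives PPV 60%.

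Two limits on this route:
- At the 29.8% hospitalization rate cited in Sample Size, the same targets need FPR 0.146 and AUC about 0.91.
- With false positives held at 10% (Sample Size goal) and sensitivity 80%, d′ = 0.842 + 1.282 = 2.12 and AUC is about 0.93.

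**Targets counted per observation period, best case.** Assumptions: 180 days of follow-up, daily scoring after a 14-day observation interval, 60% of patients with one DE, DE times uniform. The index is an oracle, constant within each patient, that flags exactly those who will have a DE.

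| τ (days) | PPV, follow-up ends at DE | PPV, follow-up continues |
|---|---|---|
| 14 | 16% | 9% |
| 30 | 33% | 20% |
| 60 | 59% | 42% |
| 90 | 79% | 65% |
| 120 | 92% | 86% |

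An oracle that also knows which DEs come early, cut at 80% sensitivity with follow-up ending at the DE, reaches 20%, 39% and 68% at 14, 30 and 60 days. A constant score with patient-level AUC 0.72 reaches 57% at 90 days and 74% at 120 days with follow-up ending at the DE (49% and 70% if it continues).

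**A realistic constant score.** Simulation: 40,000 patients, static lognormal risk with log-risk SD 0.5 to 1.0, exponential DE times calibrated to 60% in 182 days, weekly scoring.
- Per patient: AUC 0.69, 0.77 and 0.82 at SD 0.5, 0.75 and 1.0; PPV at 80% sensitivity 68%, 73% and 78%.
- Per period at 80% sensitivity: PPV 8–11% at τ = 14 days, 17–21% at 30 days, 31–37% at 60 days.
- Per period, pooled AUC at 14 days: 0.63–0.73.
- Within-patient concordance: 0.50 by construction.

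The oracle at 14 days has sensitivity 100% and a per-period FPR of 0.407, so its pooled AUC is (1 + 0.593)/2 = 0.80, again with no within-patient signal.

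**Precision of a within-patient measure.** Approximating the standard error of the mean concordance by √(1/(12m)), the 95% half-width is 1.96 × √(1/1200) = 0.057 for m = 100 DEs and 1.96 × √(1/240) = 0.127 for m = 20, which is 20% of 100.

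**The case against.** A reader might infer from the abstract that performance is defined as a contrast between patients with and without a DE, so that a static index would satisfy the plan generally. The documents do not support that. The sentence says what performance will depend on and goes on to time until the DE. The similar phrase in Performance Evaluation, "smaller differences than expected between those who experience the outcome and those who do not", is a trigger for switching to cross-validation and not a measure.

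The outcome is a DE within τ, and patients with a DE contribute earlier segments without an event. A permanently high score therefore collects false positives in those segments, and the figures above show that it misses the PPV target by a wide margin at short horizons. Change and own-baseline features are included. Even per patient, the stricter goal in Sample Size would rule out a weak static score. The choice of a supplementary within-patient summary could also sit in a fuller document that is not shown.

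Most of this stands, and it limits the point. It does not remove it. The multi-segment construction is described for the training data, and per-period scoring only for the fallback. Sample Size words its errors in terms of a person at risk, and calls its figures an ultimate goal. The article itself sets numerical targets without unit or τ, and it lists measures that cannot show the temporal effect it seeks.

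**Conclusion.** The point holds in a limited form. No listed measure distinguishes stable risk from a pre-event rise, and the unit and τ of the sensitivity and PPV targets are open.

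The size depends on the reading. Per patient at a 60% event rate, a constant score with AUC of about 0.72 meets both targets. Per observation period at 14 to 30 days, it cannot: PPV is about 8–21% for a realistic constant score and at most about 33% for one that knows exactly who will have a DE (39% if it also knows which DEs come early). At a τ of about 90 days or more the target can come back within reach, first for near-perfect static scores and at about 120 days for one with AUC 0.72. Short of the targets, a constant score can still show a pooled AUC of 0.63–0.73 and a long lead time.

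These figures rest on assumptions that the article does not give: uniform or exponential DE times, the scoring frequency, the example values of τ, binormal scores, and the spread of static risk. This is a worthwhile, inexpensive improvement and not an error that invalidates the plan.

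**What to change.** In Performance Evaluation:

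1. State that sensitivity and PPV are evaluated per observation period, at a named τ, in both the 80:20 and the cross-validation routes.
2. For patients with a DE, compare the AIDI in the τ days before the DE with the same patient's earlier windows, using concordance stratified by patient (0.5 = no warning). Report the false-alarm rate in those earlier windows.
3. State that claims of early warning or lead time rest on this comparison and not on pooled sensitivity and PPV alone.

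The cost is one extra analysis on data already collected. Reported performance may look less favourable. Precision is about ±0.06 with 100 DEs but only about ±0.13 if about 20 test DEs are available.

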**Results:**

Recruitment began in January 2023, and at the time of manuscript submission, 204 patients have been enrolled. Publication of the complete results and data from the study is expected in 2025.

**Conclusions:**

The focus on identifying predictor variables using a combination of biosensor-derived physiological features should enable the capture of heterogeneous characteristics of complications related to post–COVID-19 condition across diverse populations.

**Trial Registration:**

ClinicalTrials.gov NCT05220306; https://clinicaltrials.gov/study/NCT05220306

## Introduction

Severe complications of postacute COVID-19 infection like thrombosis, respiratory failure, and cardiac and vascular damage increase the likelihood of future morbidity and mortality in recovered patients. In one study of individuals who had been hospitalized with COVID-19, nearly a third (14,060/47,780, 29.4%) of individuals who were discharged from the hospital after acute COVID-19 were readmitted, and more than 1 in 10 (5875/47,780, 12.3%) died over a follow-up period of 140 days after discharge [1]. These events occurred at rates 4 and 8 times greater, respectively, than in the matched control group from the general population. In another study, the 6-month incidence of a new hospitalization among patients previously hospitalized with COVID-19 was found to be 29.8% [2]. SARS-CoV-2 infection can also lead to postacute development of substantial cardiac cellular abnormalities and cardiovascular clinical sequelae, including dysrhythmias, ischemic heart disease, heart failure, pericarditis, myocarditis, and thromboembolic disease [3]. Glycometabolic abnormalities are also evident in many survivors of acute COVID-19 and, in some cases, manifest as overt new-onset diabetes mellitus [4].

Risks of complications are higher among patients with comorbidities like congestive heart failure, chronic obstructive pulmonary disease, asthma, chronic kidney disease, diabetes, and hypertension [1,5,6]. Thus, although the current rate of new COVID-19 infection has dropped, the risk of morbidity, mortality, and organ dysfunction among the survivors of COVID-19 infection is high, especially among those with preexisting illnesses. Compelling evidence suggests that the pandemic may lead to new-onset kidney disease (and other noncommunicable chronic diseases including diabetes, cardiovascular disease, and neurological disease) in the millions. Given the scale and the chronic nature of several of its sequelae, post–COVID-19 condition (also known as “long COVID” or “postacute sequelae of COVID-19”) will reverberate with us for decades and will have broad and deep social and economic impact long after the COVID-19 pandemic abates [7]. Thus, it would be appropriate to infer that the next wave related to COVID-19 may not necessarily be a new strain but rather the surge of hospitalizations due to postacute complications. Developing strategies to prevent decompensation among high-risk survivors of COVID-19 has emerged as an unmet need.

One approach to the prevention of decompensation is to monitor for worsening in physiological parameters after hospital discharge. However, collecting such data longitudinally for prediction poses several challenges. First, only a limited number of parameters can be easily collected (eg, blood pressure, heart rate, oxygen saturation, etc), although additional parameters such as heart rate variability and lung function may provide additional prognostic data. Second, even if patients or families are able to collect these parameters longitudinally, there is no automated, validated method to analyze those data concurrently and provide a quantitative assessment of decompensation risk over time. These limitations hinder the sensitivity and thus the utility of current approaches to using physiologic parameters to predict decompensation risk among patients after COVID-19.

The overall objective of this study (trial registration: ClinicalTrials.gov NCT05220306) is to use a handheld, multisensor device—MouthLab, which measures 10 vital health parameters in 60 seconds—and a cloud-based proprietary engine to develop and validate the Aidar Decompensation Prediction Index (AIDI). MouthLab measures oral temperature, single-lead electrocardiogram, heart rate, breathing rate, heart rate variability, respiratory flow morphology, oxygen saturation, pulse rate, and basic lung function (forced expiratory volume in the first second and peak expiratory flow rate). The study will collect MouthLab data from patients previously hospitalized with COVID-19 (“severe COVID-19”) in order to identify decompensation predictor variables. These variables will be used to develop the AIDI to accurately predict decompensation events (DEs) related to post–COVID-19 condition. Index development will follow best practices in machine learning and algorithmic development, where the main outcome is any COVID-19–related event that leads to an emergency department (ED) visit, hospitalization, or the need for escalated care (new diagnosis or change in intervention to manage the chronic conditions). These DE cases will help inform the final set of predictor variables to develop the AIDI. In the future, early prediction and real-time risk triaging using the AIDI may support better clinical decision-making, thus preventing complications, controlling disease progression, and improving outcomes. The aim of this paper is to describe the protocol for this study to develop and validate the AIDI.

